**Methods:**

In this multisite open-label randomized controlled trial, 1920 diverse women students at 2 Canadian and 4 US universities will be randomly assigned to receive either the 12-hour IDEA^3^ (intervention arm) or standard of care (control arm: 60-minute, web-based, live-facilitated consent workshop). Outcomes are measured at baseline, 1 week, 6 months, and 12 months post intervention. SA will be assessed using the Sexual Experiences Survey-Short Form Version. Survivor self-blame and outcomes known to be mediators of EAAA’s reductions in SA will also be measured.

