### Randomization

When participants have completed their screening interview, they receive an email inviting them to complete the baseline survey (see section below on assessments for more details). The baseline survey must be completed no less than 24 hours before their first program session (or only program session for control participants). The email contains an individualized URL taking them directly to this first survey, which takes 30-45 minutes.

Randomization of the pair will occur once both participants in the pair complete their screening interview and baseline survey, and no later than 24 hours before the first (or only) session. If one member of the pair fails to complete the baseline survey, the other member of the pair will be given the choice of continuing in the study with a different partner (time permitting), rescheduling for a later intervention session, or discontinuing the research. In rare circumstances, that is, if the participant has been re-paired once or more, there is insufficient time to re-pair, or no one else is available for a new pairing, she will be individually randomized and permitted to complete the intervention by herself. Once the pair is randomized, they are sent a Zoom link for the session through REDCap. This link does not identify their random assignment. The facilitators/research assistant (RA) reveal the assignment once everyone is present in the Zoom room at the scheduled time.

The trial biostatistician is responsible for setting up the randomization protocols in REDCap. Randomization is stratified by site using permuted block sizes of 2 and 4, and participant pairs are randomized 1:1 to the IDEA^3^ program or control. Randomization occurs after baseline completion so that participation in the trial cannot be affected by knowledge of intervention assignment. The site coordinators generating the random assignment for a participant pair are not able to view the random allocation sequence.

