#### Postintervention Survey

One week after the completion of the final session for participants in the intervention arm, participants in the same recruitment cohort in both arms of the trial will be invited by email to complete the postintervention survey via the web-based REDCap platform. This survey includes the same measures used in the baseline, excluding demographic questions. It includes additional secondary outcome measures: (1) a measure of Risk Assessment and Resistance developed by Testa et al [35] built on items from Norris et al [36] and Davis et al [37], and (2) an open-ended question measuring knowledge of effective resistance strategies and willingness to use them if a man they knew tried to force them to have sex when they did not want to. It also contains “contamination questions” to determine whether and to what extent participants in the intervention arm shared information with those in the control arm, or control arm participants had IDEA^3^ content shared with them. Participants who indicate on the postintervention SES-SFV that they experienced a completed or attempted rape will also be asked follow-up questions relating to the first (and the most recent if more than one) SA (eg, the date the assault happened, her relationship to the perpetrator, etc) and these same participants will also be asked to complete the Rape Attribution Scale [38] to assess self-blame.

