### Statistical Analyses

Analyses will be performed after all participants have completed their 1-year follow-up survey. Following a modified intention-to-treat principle, a participant will be included in the analyses if they are randomized and complete one or more postrandomization surveys. The analyses will compare the incidence (ie, first occurrence) of each primary and secondary outcome between the IDEA^3^ and control groups with Kaplan-Meier failure curves (indicating the cumulative percentage of first outcomes among women in the respective groups) and log-rank tests. Participants who are lost to follow-up or drop out will have their data censored at the time of last contact. To account for the correlation between the paired observations, variance estimates will be appropriately inflated for within-pair clustering with the use of estimates of the design effect [50]. In case of baseline imbalances in participant characteristics, Cox proportional hazards regression models with a robust sandwich covariance matrix to account for the clustering will be used to compare the IDEA^3^ and control groups while controlling for the confounding factors. The literature [24,51,52] suggests that prior SA can be a modifier with respect to the effectiveness of SA resistance interventions. Therefore, intervention effects will be compared for women with and without SA histories at baseline by adding a cross-product term to the Cox regression model and testing for statistical significance. For the tertiary outcomes, which are all continuous, linear mixed models will be used to analyze the data that mirror a multilevel repeated-measures study design. A random intercept will be included in the models to account for the correlation between the paired observations, and a first-order autoregressive covariance structure will be used to characterize the interdependence of the repeated measures over time. A cross-product term between group and time will also be included in the models. Participants who are lost to follow-up or drop out can affect the validity of the group comparison if (1) the outcome is related to being lost or dropped, and (2) it is differential between groups. Therefore, baseline characteristics of women who are lost and drop out will be compared with women who complete the trial. In addition, the missing data mechanism will be formally tested [53] to determine whether it is Missing Completely at Random or missing at random. For completeness in assessing the effect of missingness, 2 additional analyses will be conducted: (1) a “per-protocol” analysis among participants who attend all sessions and respond to the 1-year SES-SFV questions; (2) multiple imputation of 5 data sets using a discriminant function for binary outcomes and Markov chain Monte Carlo for continuous outcomes, assuming the missing data mechanism is missing at random.

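### The tertiary mixed model fixes an AR(1) covariance by visit order on four unequally spaced surveys, so standard errors for change over time are wrong for the scales measured at baseline

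*Protocol article*

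**What the plan says.** The Statistical Analyses section of the protocol article sets the tertiary model: "For the tertiary outcomes, which are all continuous, linear mixed models will be used". For repeated surveys of the same woman it fixes the structure: "a first-order autoregressive covariance structure will be used to characterize the interdependence of the repeated measures over time". The only random effect it names is for partners: "A random intercept will be included in the models to account for the correlation between the paired observations". The mean model has an interaction: "A cross-product term between group and time will also be included in the models". A robust variance is named only for the time-to-event models: "Cox proportional hazards regression models with a robust sandwich covariance matrix to account for the clustering".

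The schedule is as follows.
- Abstract, Methods: "Outcomes are measured at baseline, 1 week, 6 months, and 12 months post intervention".
- Randomization: "The baseline survey must be completed no less than 24 hours before their first program session".
- Postintervention Survey: the second survey comes "One week after the completion of the final session for participants in the intervention arm".
- 6- and 12-Month Follow-Up Surveys: these are timed from baseline and shifted to avoid the summer.

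According to Baseline Survey, six tertiary scales are collected from the start: self-defense self-efficacy, perceived risk, Perceived Causes of Rape, rape myths, and the two exploratory scales. Risk detection, knowledge of resistance strategies and self-blame are first asked at 1 week.

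**The concern.** AR(1) indexes correlation by visit number. One parameter ρ serves baseline to 1 week, 1 week to 6 months and 6 to 12 months alike; ρ² serves two steps and ρ³ serves baseline to 12 months. The first gap is a few weeks and the other two are five or six months. No woman-level intercept is stated, so the model has no proper place for a woman's stable level on an attitude scale. The pair intercept can absorb only part of it, and is distorted in doing so.

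The group-by-time tests and the contrasts for change and waning take their standard errors from this covariance. Tertiary Outcomes says that mediators the program fails to move will guide its revision. Key Findings says the data will show how long effects last and whether refreshers are needed. A standard error that is too large can hide a real change; one that is too small can suggest waning or recovery that is not there.

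**Working it through.** **The plan's own figures.** The article gives no number for this model. Its total of 1676 × 1.031 / 0.90 = 1919.95, rounded to 1920, is for the primary outcome and does not use this covariance. The tertiary power statement is for a group difference at 1 week and uses no within-woman correlation.

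**Inputs.** From the article: four surveys, a pair intercept, AR(1). Assumed: the first gap is 1 month (1.5 months as a check), with later surveys at 6 and 12 months; variance is 1 at each visit; cross-partner correlation is 0.03 at all visits, close to the 0.031 in Sample Size Considerations, which is for the primary outcome; data are complete and the group-by-time mean is saturated. The within-woman correlations are assumed because the article gives none.

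**Method.** For each assumed true covariance of a pair (8×8, Σ), find the pair-intercept variance τ, residual variance s² and ρ that minimise log|V| + tr(V⁻¹Σ). This is where the stated model settles in large samples. The pair intercept cancels from a change, so for two visits k steps apart with true correlation r:

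model SE / true SE = √[ s²(1 − ρᵏ) / (1 − r) ]

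For a group difference at one visit the ratio is √[(s² + 2τ) / 1.03].

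**Scenarios (first gap 1 month).**
- A: correlation decays with real time, 0.5 at 6 months. Fit: s² = 0.980, ρ = 0.644, τ = 0.020.
- A2: the same with 0.7 at 6 months. Fit: 0.976, 0.790, 0.024.
- B: stable trait 0.50, decaying part 0.35 (its own 6-month correlation 0.3), measurement error 0.15. Fit: 0.896, 0.636, 0.105.
- D: trait 0.40, decaying part 0.30 (same decay), error 0.30. Fit: 0.894, 0.496, 0.107.
- C: constant correlation 0.6. Fit: 0.855, 0.533, 0.148.

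In B, C and D the fitted τ is three to five times the assumed 0.03: the pair intercept is absorbing the missing woman-level effect.

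**Worked line, scenario A.** True adjacent correlations are 0.5^(1/6) = 0.89, 0.5^(5/6) = 0.56 and 0.50; the model gives 0.64 to all three.
- 1 week minus baseline: √[0.980 × 0.356 / 0.109] = 1.79.
- 12 minus 6 months: √[0.980 × 0.356 / 0.50] = 0.84.

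**Model SE / true SE**

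| Contrast | A | A2 | B | D | C |
|---|---|---|---|---|---|
| 1 week − baseline | 1.79 | 1.88 | 1.24 | 1.13 | 1.00 |
| 6 months − baseline | 1.07 | 1.11 | 1.16 | 1.15 | 1.24 |
| 12 months − baseline | 0.98 | 0.98 | 1.19 | 1.17 | 1.35 |
| 12 months − 1 week | 0.89 | 0.87 | 1.08 | 1.09 | 1.24 |
| 12 − 6 months | 0.84 | 0.83 | 0.91 | 0.94 | 1.00 |
| Single visit | 1.00 | 1.00 | 1.04 | 1.04 | 1.06 |

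**Size of a nominal 5% test**, 2[1 − Φ(1.96 × ratio)]:
- 1 week minus baseline: below 0.1% (A), 1.5% (B), 2.7% (D), 5.0% (C).
- 12 months minus baseline: 5.5%, 1.9%, 2.2%, 0.8%.
- 12 minus 6 months: 10.1%, 7.5%, 6.5%, 5.0%.

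**Sensitivity.** With a first gap of 1.5 months, 1 week minus baseline falls to 1.49 (A) and 1.17 (B). With trait 0.4 and 15% error it is 1.28 (1-month gap) or 1.20 (1.5 months). Raising the cross-partner correlation to 0.10 moves a ratio by at most about 0.03. At constant correlation 0.7 the 12-month change ratio reaches 1.44.

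**The case against.** **Size.** A reader might infer that the early-change standard error is inflated by half or more and that intervals for 12 months minus 1 week undercover. Both need correlation that decays with time and almost no measurement error (A, A2). Self-report scales carry error. With 15-30% of it, the first effect shrinks to roughly 10-28% and the second reverses to mild conservatism. This objection stands. What survives under decay is the understated standard error for 12 minus 6 months.

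**Scope.** Risk detection and knowledge of resistance strategies, two of the three primary mediators, have no baseline, and their gaps of about 5 and 6 months are nearly equal. Self-blame is asked only of women reporting attempted or completed rape. This also stands, and limits the spacing problem to the six scales asked at baseline.

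**The powered comparison.** Tertiary power above 99% is claimed for single-visit differences at 1 week, where the ratio is 1.00 to 1.06. Revision of the program could be decided on those. True, but the stated model also includes the group-by-time term, and durability is a question about change.

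**Bias.** A reader might infer that the estimated effects are biased. With complete data they are not. With missing visits the likelihood borrows through the wrong covariance and estimates could shift, but this was not quantified, and planned loss is at most 10%. The planned multiple imputation is a partial check on estimates; it does not repair standard errors if the same AR(1) model is fitted to each imputed set.

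**Condensed article.** A separate analysis plan might define AR(1) in continuous time or add a woman-level intercept. The article, however, states a specific structure and assigns the intercept to the pair. That is a stated choice that misfits the schedule, not a detail left out.

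**Conclusion.** The point holds for the six tertiary scales measured at all four surveys. AR(1) by visit order, with only a pair intercept, misstates the standard error of at least one change contrast under every covariance tried. The direction is mixed and the size rests on assumed correlations: over the tabulated scenarios the ratio is 1.00-1.88 for 1 week minus baseline, 0.98-1.35 for 12 months minus baseline, 0.87-1.24 for 12 months minus 1 week, and 0.83-1.00 for 12 minus 6 months. With realistic measurement error most departures are about 5-20%: conservative for change from baseline, mildly anti-conservative for 12 minus 6 months.

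The documents do not support a reading that the trial's main result is at risk. The log-rank and Cox analyses and the sample size do not use this covariance. It is worth correcting because it is a fixed choice that contradicts the trial's own schedule and can be changed before analysis begins.

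**What to change.** Replace AR(1) with an unstructured within-woman covariance over the visits at which each outcome is measured, and keep the pair random intercept. For the baseline scales this is 4×4: 4 × 5 / 2 = 10 parameters, against 2 for AR(1). Even the 683 women enrolled by August 2025 would support that. Outcomes first measured at 1 week need a smaller matrix. In every scenario above the ratio becomes 1.00.

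Self-blame will be sparse. At the assumed rates, 960 × 0.061 + 960 × 0.098 ≈ 59 + 94 = 153 women would report completed rape over the year before loss, spread over three surveys, plus those with attempted rape only. There, use a woman-level random intercept, add a continuous-time correlation in actual days if needed, and use robust standard errors clustered on pair.

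The cost is a few more covariance parameters and one changed model option. Analyses start only after all 1-year follow-up is complete, so the change can be pre-specified.

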### Outcome Assessments

Web-based surveys will be administered to participants at 4 time-points as explained in the following subsections.

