#### Baseline Survey

After completing the screening interview and giving consent, participants are invited to complete the baseline survey. The survey includes a number of demographic questions (eg, year of study, age, ethnicity, sex assigned at birth, gender identity, sexual identity, sexual orientation, current relationship status, number of sexual partners, and age of first sexual contact), primary outcome assessment (Sexual Experiences Survey-Short Form Victimization [SES-SFV]) [28], secondary outcomes scheduled for the baseline (Self-defense Self-efficacy Scale) [29], perceived risk for acquaintance SA [30] (1 item), the Perceived Causes of Rape Scale [31], and the Updated Illinois Rape Myth Acceptance Scale [32], and tertiary outcomes (Acceptance of Sexualized Aggression Scale [33], 13 items from the Sexual and Reproductive Empowerment Scale [34]).

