### Sample Size Considerations

In calculating the sample size for the proposed trial, we used estimates of the 1-year incidences and difference in completed rape from the previous trial (9.8% control vs 5.2% EAAA=4.6% difference [5]). However, we conservatively powered the trial so we can still detect meaningful differences even if IDEA^3^ is less efficacious than in-person EAAA, that is, it achieves 80% of the previously observed difference (80% of 4.6%=3.7%). Therefore, assuming 1-year incidences of completed rape in the proposed trial of 9.8% in the control group versus 6.1% in the intervention group, a sample size of 1676 will have 80% power to detect an absolute difference of 3.7% (relative risk reduction of 37.75%) at a 2-sided 5% level of significance. As participants in the IDEA^3^ sessions will be in pairs, the sample size is further inflated by a design effect of 1.031, based on a within-pair correlation of 0.031 from the previous trial. Including an estimated maximum 10% lost-to-follow-up, a total of 1920 participants will be enrolled in the trial (1920=1676×1.031/0.90). Using estimates for the secondary outcomes from the previous trial [5] and similarly, assuming 80% efficacy compared with the in-person intervention, the proposed sample size yields 97% power for comparing 1-year differences in attempted rape (9.3% vs 4.6%), 92% power for sexual coercion (22.6% vs 16.1%), and 99% power for sexual contact (39.1% vs 28.5%). Using estimates for the tertiary outcomes from the previous trial [21] and similarly, assuming 80% less efficacy, the proposed sample size yields > 99% power for comparing 1-week postintervention group differences in risk perception (Cohen *d* 0.58), rape myths (Cohen *d*=0.48), risk detection (Cohen *d*=0.54), and self-defense self-efficacy (Cohen *d*=0.64).

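### The tertiary mixed model states no adjustment for the pre-randomization baseline score, so six scales are estimated less precisely than the data allow

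*Protocol article*

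**What the plan says.** The Statistical Analyses section of the protocol article describes the tertiary model in some detail: "linear mixed models will be used to analyze the data that mirror a multilevel repeated-measures study design". On clustering it says: "A random intercept will be included in the models to account for the correlation between the paired observations". On the visits it says: "a first-order autoregressive covariance structure will be used to characterize the interdependence of the repeated measures over time". It then adds: "A cross-product term between group and time will also be included in the models". For these models it names no baseline covariate and no constraint on the baseline means. The only covariate adjustment in the section belongs to the Cox models for the primary and secondary outcomes, and is conditional on an observed imbalance.

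On timing, Outcome Assessments says: "Web-based surveys will be administered to participants at 4 time-points". The first of these is the baseline survey, and the Randomization section places it before allocation: "Randomization occurs after baseline completion so that participation in the trial cannot be affected by knowledge of intervention assignment".

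The Baseline Survey section lists four scales under "secondary outcomes scheduled for the baseline (Self-defense Self-efficacy Scale" and what follows: self-efficacy, perceived risk, Perceived Causes of Rape and rape myth acceptance. It adds two exploratory scales, on acceptance of sexualized aggression and on sexual empowerment. Outcome Measures classes all six as tertiary, and that classification is used here. The other three tertiary outcomes are first measured after the intervention (Postintervention Survey; 6- and 12-Month Follow-Up Surveys).

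Sample Size Considerations states power for "1-week postintervention group differences in risk perception" and three further scales.

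**The concern.** Because baseline is measured before allocation, the arms have equal expected scores there. A repeated-measures model with a group-by-time term and nothing further ordinarily estimates a separate baseline mean for each arm, and so does not use that equality. The treatment effect is then either a difference in change from baseline, which carries the full sampling error of the baseline scores, or a group difference at a visit, which ignores them. A baseline-adjusted estimate is more precise than both whenever r lies strictly between 0 and 1.

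Two intended uses of the results depend on this precision. Under Tertiary Outcomes, program material is to be strengthened for mediators on which the intervention shows no significant effect, so an imprecise estimate can prompt revision that is not needed. Under Key Findings in the Discussion, the data are to show how long effects last and whether refreshers are needed. That concerns the later visits, where effects may be smaller than at 1 week.

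**Working it through.** **The plan's own figures.** Inputs from Sample Size Considerations: 9.8% versus 6.1%, two-sided 5%, 80% power, design effect 1.031, 10% loss.

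- The two-proportion formula (pooled variance, no continuity correction) gives 838 per arm, or 1676 in total. 1676 × 1.031 / 0.90 = 1919.95, so 1920.
- Effective size for a continuous outcome is 1920 × 0.90 / 1.031 / 2 = 838 per arm. In SD units the standard error of a visit difference is √(2/838) = 0.0489.
- The listed d values are 0.48 to 0.64. At 0.48, and at 0.8 × 0.48 = 0.384, power exceeds 99.9%. The stated figure of above 99% is reproduced, reading the efficacy reduction as 80% of the earlier effect, as for the other outcomes.

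**Variance of the arm difference, in units of the visit-difference variance.** Assumptions: complete data, equal variances at each visit, r the baseline-to-visit correlation (not given in the article).

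- Group difference at the visit: 1
- Change-from-baseline interaction: 2(1−r)
- Baseline-adjusted, or arms held to a common baseline mean: 1−r²
- Adjusted relative to change: (1−r²) / [2(1−r)] = (1+r)/2
- Adjusted relative to visit difference: 1−r²

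| assumed r | change | visit | adjusted | reduction vs change | reduction vs visit |
|---|---|---|---|---|---|
| 0.3 | 1.40 | 1 | 0.91 | 35% | 9% |
| 0.5 | 1.00 | 1 | 0.75 | 25% | 25% |
| 0.7 | 0.60 | 1 | 0.51 | 15% | 49% |

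**Which visit loses most.** Under the planned AR(1) structure, taken by visit order with adjacent correlation ρ, r is ρ at 1 week, ρ² at 6 months and ρ³ at 12 months. The standard-error ratios to the adjusted estimate are √(2/(1+r)) for change and 1/√(1−r²) for the visit difference.

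| assumed ρ | change: 1 wk / 6 mo / 12 mo | visit: 1 wk / 6 mo / 12 mo |
|---|---|---|
| 0.5 | 1.155 / 1.265 / 1.333 | 1.155 / 1.033 / 1.008 |
| 0.7 | 1.085 / 1.159 / 1.220 | 1.400 / 1.147 / 1.065 |
| 0.9 | 1.026 / 1.051 / 1.076 | 2.294 / 1.705 / 1.461 |

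The ordering over visits is opposite for the two contrasts.

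**Effect on power.** The largest standard error for the change contrast in these scenarios is 0.0646 (ρ = 0.5, 12 months). With d = 0.384, 0.384 / 0.0646 − 1.96 = 3.98, so power is still above 99.9%. A loss shows only for effects well below those listed. With an assumed d of 0.15 at 12 months and ρ = 0.7, power is 76.4% for the change contrast, 86.7% for the visit difference and 90.5% with baseline adjustment.

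**The case against.** The strongest reply is that the article does not state the model being criticized. It does not say that baseline is one of the modelled responses, that the arm means are free there, or that the effect is read from the cross-product term. A group-by-time term also fits a model with baseline as a covariate and the follow-up visits as outcomes. A condensed article may leave such coding to an analysis plan that is not shown.

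This limits the wording of the point but does not remove it. The published specification names the random effect, the covariance structure and the interaction, and on its ordinary reading it contains no adjustment. Both contrasts it could yield are less precise than the adjusted one.

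Several stronger readings that a reader might infer are not supported:

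- **That the baseline scores are wasted.** A change contrast uses them, though inefficiently. Only the visit difference ignores them.
- **That the loss is worst at 12 months.** This holds for the change contrast under AR(1). For the visit difference, which is closest to the wording in Sample Size Considerations, it is worst at 1 week.
- **That the analysis is biased or underpowered.** Neither contrast is biased by the omission, and the stated 1-week power is unaffected.
- **That all the mediators are affected.** Risk detection, knowledge and willingness, and self-blame have no baseline measure. The first two are among the three that the article calls primary mediators, so only self-efficacy in that group can gain.
- **That the effect will be judged by one overall interaction test.** The article does not say so.

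A last objection concerns the remedy. The analysis set is restricted to randomized participants with at least one later survey. Equal baseline means are guaranteed in expectation for everyone randomized. In that subset they also require that non-response not differ between arms in a way related to the baseline score. This stands, and it shapes the fix.

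**Conclusion.** The point holds as a matter of precision on six tertiary scales. As written, the model states no use of the equality of the arms at baseline. At an assumed r of 0.5, adjustment would lower the variance by 25% against either unadjusted contrast. For r from 0.3 to 0.7 the reduction is 35% down to 15% against the change contrast, and 9% up to 49% against the visit difference. These sizes rest on assumed correlations, complete data and equal variances.

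The practical effect is small for effects of the size the article expects at 1 week. It could matter for smaller effects at 6 and 12 months, which bear on the decisions about revision and refreshers. The outcomes are tertiary, so this is a worthwhile improvement and does not threaten the trial's main conclusion.

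**What to change.** For the six scales with a baseline measure, model the 1-week, 6-month and 12-month scores as outcomes, with the baseline score as a covariate and group-by-visit terms. Keep the planned allowance for pairs and repeated measures. An alternative is to model all four visits with the arms held to a common baseline mean. In that case include every randomized participant with a baseline score, so that the constraint rests on randomization and not on who responded later.

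Report the adjusted arm difference with its confidence interval at each follow-up visit, and name the 1-week difference as the lead contrast, in line with Sample Size Considerations. State that the three outcomes without a baseline measure are analyzed without this adjustment.

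The cost is a change to the model wording. No new data are needed, and because analysis waits until all 1-year surveys are complete, the change can still be prespecified.

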### Outcome Measures

#### Primary Outcomes

The primary aim of the trial is to test whether IDEA^3^ can reduce the 1-year incidence of completed rape among women attending university in Canada and the United States. Completed rape will have occurred when a participant indicates she has had at least one experience of threatened, forced, or drugged completed (not attempted) sexual activity (oral, anal, or vaginal intercourse)—answered “once” or more to any of 9 items (2c-e, 3c-e, and 4c-e) in the period between the last outcome measurement and the current day (SES-SFV). Dates of occurrences will be recorded using a calendar function to allow time-to-event analyses. The SES-SFV has been used in very large university and college and community samples and is considered the gold standard. We use the gender-specific version (male perpetrator) due to the focus of the intervention. Responses on the scale are stable across administrations [28] and are comparable to those received through interviews [45]. The validity of the scale has been demonstrated in many published studies [28,47]. Predictive validity has been demonstrated with correlations between sexual victimization and variables predicted to be influenced by it, such as trauma symptoms [28].

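### Five imputed data sets are too few for the supplementary missing-data analysis, and its yes/no outcome needs a named comparator: the 12-month Kaplan-Meier risk difference

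*Protocol article*

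**What the plan says.** All of this is in the protocol article, mainly under Statistical Analyses.

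- The primary and secondary outcomes are compared "with Kaplan-Meier failure curves (indicating the cumulative percentage of first outcomes among women in the respective groups) and log-rank tests". Under Primary Outcomes, event dates are collected for this purpose: "Dates of occurrences will be recorded using a calendar function to allow time-to-event analyses".
- Incomplete follow-up is handled by censoring: "Participants who are lost to follow-up or drop out will have their data censored at the time of last contact".
- Missing data are then examined further: "For completeness in assessing the effect of missingness, 2 additional analyses will be conducted". One is a per-protocol analysis. The other is "multiple imputation of 5 data sets using a discriminant function for binary outcomes", with Markov chain Monte Carlo for continuous outcomes, "assuming the missing data mechanism is missing at random".
- The aim is stated on the risk scale, to "test whether IDEA^3^ can reduce the 1-year incidence of completed rape", and Sample Size Considerations uses 1-year proportions of 9.8% and 6.1%.

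The number of imputations is therefore a stated choice. The article does not name the quantity to be estimated from the imputed data sets, or the observed-data result it will be set beside.

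**The concern.** Two things looked weak.

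**Number of imputations.** Five is usually defended by relative efficiency, which is high here. That measure describes the average variance of the pooled estimate. It does not say how far one reported p-value moves when the same data are imputed again with another seed. If the result is close to 0.05, the seed could decide which side of the line it falls on.

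**Imputed quantity.** The primary analysis needs a time for each woman, either to event or to censoring. An imputed yes/no status has none, so the completed data sets cannot enter the log-rank test or Cox model as described. A difference between the two results would then mix the effect of missing data with a change of scale and test.

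This analysis is the only one in the article that fills in missing outcomes. The per-protocol analysis instead restricts to women who attended every session and answered the 1-year questions.

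**Working it through.** **Inputs from the article.** 1-year risks 9.8% and 6.1%; two-sided 5% level; 80% power; 1:1 allocation; design effect 1.031; maximum loss 10%; 1920 enrolled; m = 5 imputations.

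**The plan's own figure.** With the pooled-variance formula for two proportions,

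n per arm = [1.960·√(2 × 0.0795 × 0.9205) + 0.842·√(0.098 × 0.902 + 0.061 × 0.939)]² / 0.037² = 838, so 1676 in total.

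1676 × 1.031 / 0.90 = 1919.95, so 1920. Both stated figures reproduce.

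**Analytic check.** Let FMI be the fraction of missing information, taken as 0.10 at 10% loss (the simulation below gives about 0.10).

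- Relative efficiency = 1/(1 + FMI/m) = 1/(1 + 0.10/5) = 98.0%.
- Seed noise as a share of the standard error = √(FMI/m): √(0.10/5) = 14% at m = 5, √(0.10/50) = 4.5% at m = 50, √(0.10/100) = 3.2% at m = 100.

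Both statements hold together: little efficiency is lost, yet the z-statistic moves by about 0.14 (one SD) from seed to seed.

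**Simulation.** Each fixed data set was imputed with 20,000 seeds. There were 960 women per arm, with 864 observed and 96 missing at 10% loss. Status was imputed within arm from a posterior draw of the risk. The risk difference was pooled by Rubin's rules with a t reference, and its variance was multiplied by 1.031.

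| Observed events (control vs IDEA3) | Missing | m | Middle 95% of p over seeds | Seeds with p ≥ 0.05 |
|---|---|---|---|---|
| 85 vs 53 (planned effect) | 10% | 5 | 0.0019–0.0172 | about 0% |
| 85 vs 53 | 10% | 100 | 0.0040–0.0063 | 0% |
| 85 vs 61 (borderline) | 10% | 5 | 0.020–0.089 | 34% |
| 85 vs 61 | 10% | 50 | 0.032–0.051 | 4% |
| 85 vs 61 | 10% | 100 | 0.034–0.048 | 0.5% |
| 75 vs 47 (planned effect) | 20%, assumed | 5 | 0.002–0.051 | 3% |
| 75 vs 47 | 20%, assumed | 100 | 0.0065–0.0125 | 0% |

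Repeating the first row moved its upper end to about 0.018. At the planned effect and m = 5, the seed SD of the risk difference is 0.18 points against a standard error of 1.33 points (0.18/1.33 = 14%), which matches the formula.

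The two 10% cases differ because of their distance from the critical value. At 85 vs 53, z is about 2.80, and (2.80 − 1.96)/0.14 is 6 seed SDs. At 85 vs 61, z is about 2.05, and (2.05 − 1.96)/0.14 is about 0.6.

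Averaged over trials drawn at the planned rates, two seeds disagree on significance about 5% of the time with m = 5 and about 1.6% with m = 50.

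**Scale.** The planned risks imply:

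- risk difference: 9.8% − 6.1% = 3.7 points
- risk ratio: 0.061/0.098 = 0.622
- odds ratio: (0.061/0.939)/(0.098/0.902) = 0.598
- hazard ratio, if hazards are proportional: ln(1 − 0.061)/ln(1 − 0.098) = 0.610

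A status-based estimate is not the hazard ratio. The risk difference, however, is also what the Kaplan-Meier curves give at 12 months.

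**The case against.** The strongest reply is that this analysis is supplementary, that no rule lets its p-value override the primary result, and that at the design effect the seed does not change the conclusion. All of that stands.

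The simulation also probably overstates the noise. It treats every missing woman as having no outcome information and uses no predictors. The article's inclusion rule is that "a participant will be included in the analyses if they are randomized and complete one or more postrandomization surveys". Read literally, the women being imputed would have some follow-up. Under Differential Dropout, the article also plans a short survey of only the assault items for non-responders at 6 and 12 months. Both would lower the fraction of missing information. The 20% rows exceed the plan's stated maximum.

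Three stronger readings are tempting, and the article does not support them.

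- *The missing-data check as a whole depends on the seed.* The noise matters only near p = 0.05, or if loss runs clearly above 10%.
- *The imputed and primary results cannot be compared at all.* The aim and the sample size are both on the 1-year risk scale, and the Kaplan-Meier curves supply that risk. Only the log-rank p-value and the hazard ratio lack a like-for-like counterpart.
- *Event times must be imputed.* That is one possible design, but not one a supplementary analysis requires. The covariates and form of the imputation model are ordinary analysis-plan detail, so their absence from a condensed article is no fault.

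What survives the reply is that five is a fixed choice in the text, and a larger number is better at almost no cost.

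**Conclusion.** The point holds as a minor, nearly free improvement. Five imputations leave seed noise of about 14% of the standard error at 10% loss. That is harmless at the planned effect. In the borderline example it puts about a third of seeds above 0.05, against about 4% at m = 50 and under 1% at m = 100. Separately, the yes/no imputation matches the primary analysis only on the 12-month risk scale, and the article does not name that comparison.

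The figures assume 960 women per arm, no partial follow-up among those missing, no covariates in the imputation model, and pairing represented only by the 1.031 factor. The primary test, the sample size of 1920 and the power are untouched.

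**What to change.** Under Statistical Analyses:

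1. Replace the five data sets with at least 50, preferably 100, and state that the seed is set in advance.
2. Name the between-arm difference in 1-year risk as the quantity estimated from the imputed data, and report it beside the 12-month Kaplan-Meier risk difference from the observed data.

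This takes one or two sentences and a few minutes of computing, with no change to data collection. The article gives May 2027 as the end of data collection, so the change can still be made before analysis.
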